### 2.15. Methods for any additional analyses

A descriptive analysis of the AEs recorded throughout the trial will be carried out for patients enrolled in the safety analysis set.

### 2.16. Analysis population and missing data definition of analysis population relating to protocol nonadherence and any statistical methods to handle missing data

In case of missing data, imputation will be made considering the treatment effects’ estimator is not biased and that an increase in type I error has been avoided. However, assuming that the cognitive impairment will slow down and aiming to ensure the trial’s internal sensitivity (in case of expecting a different evolution of one of the experimental groups), the last observation carried forward technique seems to be a conservative approach to the matter.

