## 1. Introduction

### 1.1. Background and rationale

Niemann-Pick disease Type C (NPC) is a genetic, neurodegenerative disorder with a life expectancy ranging between 1 – and 30 years after diagnosis. From a clinical perspective, NPC usually affects the viscera (splenomegaly and/or hepatomegaly), but it is, above all, a neurological disease. It is a progressive disease without curative treatment and with only 1 treatment approved to date – with limited efficacy (Miglustat, Zavesca®). In 2019, adult-onset NPC prevalence in Spain was 27 patients, of which ten are being treated at Bellvitge University Hospital (BUH).

The disease is classified according to the age of onset of the neurological symptoms in: early infantile (before 2 years of age); late infantile (between 3 and 5 years of age); early juvenile (between 5 and 14 years of age); late juvenile (between 14 and 16 years of age); and adult (from 16 years of age onwards).

The clinical presentation includes psychomotor development regression, epilepsy, ataxia, vertical supranuclear ophthalmoplegia, bulbar syndrome, dystonia, splenomegaly, cognitive impairment, behavioral disorders, and symptoms of psychiatric disorders, with behavioral/cognitive symptoms being most common in adults. Altogether, these symptoms point towards synaptic changes as a key element in disease development, similar to other dementias (e.g., Alzheimer’s), where cognitive impairment correlates with the loss of synapses.

In 95% of the cases, genetic mutations in the NPC1 protein are responsible for disease development. The NPC1 protein is involved in the intracellular transport of cholesterol.^[1–3]^ From a cellular and molecular perspective, one of the main hallmarks of NPC is the accumulation of cholesterol and sphingolipids in lysosomal compartments, where NPC1 is found.^[4]^ Although lipid accumulation occurs in all cell types, neurons are especially vulnerable to NPC1 deficiency, suggesting that neuronal function is especially related to this protein. Also, NPC1 is found not only in cell bodies, where endosomes and lysosomes are highly abundant,^[5]^ but also in axon terminals and synaptosomes,^[6,7]^ pointing towards a synaptic role from NPC1 other than participating in the lysosomal degradation pathway.

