### 1.3. Objectives

The primary, secondary, and safety objectives are summarized in Table 1.

**Table 1 T1:** Summarized study objectives.

Primary Objective	
•To evaluate the efficacy* and safety of EFV at an oral dose of 25 mg/d, in addition to standard treatment, in patients diagnosed with adult or late juvenile-onset NPC with cognitive impairment.	
*Note: Given that adult or late juvenile-onset NPC is rare and causes progressive cognitive impairment, treatment with EFV will be considered effective if it “slows down or stops cognitive impairment in patients diagnosed with adult or late juvenile-onset NPC with cognitive impairment.” Meaning, it is hoped that after 1 year of treatment, these patients remain at the baseline with respect to cognitive impairment.	
Secondary objectives	
**Clinical**	• Neurological: To evaluate the change in the following questionnaires/scales:
	SARA
	EAT-10 score.
	PDS
	• Neuropsychological (protocol used in clinical practice): To evaluate the change in the following questionnaires/scales:
	CDR-SoB
	Verbal memory: FCSRT
	a-BT
	Verbal fluency: Semantic and phonetic cues
	TMT A and B
	STROOP
	WAIS and the block design, symbol search and vocabulary subtests (WAIS-III/WAIS-IV)
	BNT, and the Naming and Semantic Knowledge subtests
	JLO
	DEX
	NPI
	AES
	BDI
	C-SSRS
**Biological**	• To evaluate the change in functional and imaging biomarkers related to NPC:
	^18^FDG PET—scan
	Brain MRI
	Abdominal ultrasound
	Oculography
	• Evaluate the change in biochemical biomarkers related to NPC:
	Oxysterols
	Lyso-SM-509
	24-OH-Cholesterol
	Beta-Amyloid, Tau, and phosphorylated Tau
**Safety**	• To evaluate the safety of EFV in patients diagnosed with adult or late juvenile-onset NPC with cognitive impairment.

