	• Changes in the liver function panel

8 FDG PET—scan = ^18^Fluorodeoxyglucose Positron emission tomography scan, a-BT = abbreviated Barcelona test, AES = apathy evaluation scale, BDI = Beck’s depression inventory, BNT = Boston naming test, CDR-SoB = clinical dementia rating scale-sum of boxes, C-SSRS = Columbia suicide severity rating scale, DEX = dysexecutive questionnaire, EAT-10 = the eating assessment tool score, EFV = efavirenz, FCSRT = free and cued selective reminding test, JLO = judgement of line orientation test, MRI = magnetic resonance imaging, NPC = Niemann-Pick disease type C, NPI = neuropsychiatric inventory, PDS = Pineda disability scale, SARA = scale for the assessment and rating of ataxia, STROOP = Stroop color and word test, TMT = trail making test, WAIS = Wechsler adult intelligence scale.

A *deterioration in the CDR-SoB* is defined as an increase of ≥ 2 points at 52 weeks of starting treatment with EFV relative to baseline.

A *deterioration in verbal memory* is defined as a decrease of ≥ 1 in the standard deviation (SD) at 52 weeks of starting treatment with EFV relative to baseline.

A *deterioration in the executive function* is defined as a decrease of ≥ 1 in the SD (in at least 2 of the 5 tests performed) at 52 weeks of starting treatment with EFV relative to baseline.

A patient will be considered a responder (no decay in cognitive performance) if there is no deterioration in at least 2 of the 3 assessed items at 52 weeks of starting treatment with EFV relative to baseline.

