## 3. Discussion

NPC is a complex orphan disease, consisting of an unmet medical need for patients suffering from it. Although there are over 20 ongoing studies on NPC registered in the ClinicalTrials.gov database, conducting clinical trials for assessing new therapeutic options can be quite challenging, given the disease’s low prevalence. Different therapeutic approaches are under study (e.g., Miglustat, Arimoclomol, N-Acetyl-L-Leucine), but, to the best of our knowledge, this is the first clinical trial studying the effects of EFV in adult- and late-juvenile-onset NPC.

As mentioned before, neuronal cholesterol metabolism is key for LTP, which is a major event for synaptic plasticity. The enzyme CYP46A1 hydroxylates the cholesterol and mediates the main pathway for its degradation in the brain.^[9,10]^ Given that NPC1 binds cholesterol and participates in its intracellular mobilization, we hypothesized that NPC1 would have a synapse-specific role in redistributing cholesterol and mobilizing CYP46A1 to the synaptic membrane required for LTP. We believe that the capacity of EFV to activate the CYP46A1 could compensate for NPC1 deficiency and correct synaptic changes, therefore compensating cognitive and psychiatric alterations in patients with NPC. This hypothesis is supported by preclinical data^[12,14]^ suggesting that low-dose EFV may be a promising alternative for NPC patients.

On the other hand, this study has limitations. First, the already mentioned small sample size due to the disease’s low prevalence. Therefore, interpreting the results may be tough, given that we cannot safely exclude that a given outcome happened by chance. Second, it has a single-arm design (absence of a control group). Although justifiable by the natural history of the disease, the unexpectedness of spontaneous improvement, and the lack of expected placebo effects, this type of design has idiosyncratic limitations since it could be argued that responders would have responded equally if treated only with SoC. Furthermore, the absence of a frame of reference for comparison could also make the results hard to interpret.

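### Last observation carried forward is called conservative, but with a progressive disease, a non-deterioration endpoint and no control arm it leans toward efficacy whenever week-52 data are missing

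*Protocol article*

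**What the plan says.** Section 2.16 of the protocol article first sets a condition: "imputation will be made considering the treatment effects’ estimator is not biased and that an increase in type I error has been avoided". It then argues, "assuming that the cognitive impairment will slow down", that "the last observation carried forward technique seems to be a conservative approach to the matter". No other technique is named. The reasoning also mentions one of several experimental groups, although section 2.10.1 describes a single-arm trial.

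The setting comes from other sections:

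- Section 1.1 on the disease: "It is a progressive disease without curative treatment". The Discussion justifies the single arm partly by "the natural history of the disease, the unexpectedness of spontaneous improvement".
- Table 1 (section 1.3) on success: "it is hoped that after 1 year of treatment, these patients remain at the baseline with respect to cognitive impairment".
- Section 2.7, under Table 2: a patient is a responder "if there is no deterioration in at least 2 of the 3 assessed items at 52 weeks of starting treatment". The items are CDR-SoB (deterioration is a rise of 2 points or more), verbal memory (a fall of 1 SD or more) and executive function (a fall of 1 SD or more in at least 2 of 5 tests).
- Table 3 (section 2.7.1): the neuropsychological battery is scheduled at visit 1, visit 4 (week 26) and visit 6 (week 52) only.
- Section 2.14: the primary outcome is analysed by ANCOVA of week-52 cognitive performance.

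**The concern.** An imputation rule is conservative if its errors go against the claim being tested. Here the claim is that patients stay where they started. Carrying an earlier score forward in a declining disease replaces the unseen week-52 value with an earlier, usually better one, so the errors favour the claim.

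The argument offered for the rule is circular. It assumes that decline will slow, which is what the trial sets out to show. If efavirenz does nothing, that assumption fails and the rule manufactures stability. With no comparator, there is no second arm in which the same bias could offset it.

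The bias grows with the number of patients who leave or become untestable. Section 2.4 foresees stopping for unacceptable risk, withdrawn consent and loss to follow-up, and a treatment that fails or is poorly tolerated would lose more patients in these ways. With 14 patients, each one counts.

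**Working it through.** The protocol states no dropout rate, response rate, alpha or power, so there is no figure to reproduce. N = 14 (section 2.8), the visit times and the thresholds come from the document. Every response rate, dropout count, decline and SD below is an assumption.

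**1. Logic by time of loss**

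- Lost before week 26: only the baseline battery exists. Carried forward, change = 0 on all three items, no threshold is met, and the patient is a responder with certainty.
- Lost or untestable after week 26: the week-26 score stands in for week 52. About half a year of decline is compared with thresholds set for a year. Response is more likely but not certain: a patient already deteriorated on two items at week 26 stays a non-responder.
- Week-52 battery complete: no imputation and no bias.

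**2. Responder rate with early losses**

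Assume 60% response in completers and 3 of 14 lost before week 26.

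- Carried forward: (0.6 × 11 + 3)/14 = 9.6/14 = 68.6%.
- Truth if all three would have deteriorated: 0.6 × 11/14 = 6.6/14 = 47.1%.
- Truth if all three would have responded like completers: 0.6 × 14/14 = 60%.

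The bias is 68.6 − 60 = 8.6 points at the low end and 68.6 − 47.1 = 21.4 points (3/14) at the high end. Per early loss that is 0.4/14 = 2.9 points to 1/14 = 7.1 points.

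The high-end comparison at other assumed completer rates, still with 3 early losses:

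| Completer rate | Carried forward | Missing = non-responder |
|---|---|---|
| 30% | 45.0% | 23.6% |
| 50% | 60.7% | 39.3% |
| 70% | 76.4% | 55.0% |

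**3. Carrying week 26 forward**

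This is a simulation of linear decline on the three items with a shared patient progression factor. Between-patient SD of yearly decline was 1.0 CDR-SoB points and 0.5 SD units; measurement noise was 0.5 and 0.4.

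| Mean 52-week decline (CDR-SoB; SD units) | True responders | Scored from week 26 | Scored from baseline |
|---|---|---|---|
| 1; 0.5 | 79% | 98% | 100% |
| 2; 1 | 44% | 91% | 100% |
| 3; 1.5 | 14% | 71% | 100% |

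These columns describe patients who are carried forward, not the whole trial. If only the fastest-declining 20% are lost in the middle row, the trial's rate moves from 44% to 57% (week 26 carried) or 64% (baseline carried).

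**4. Type I error under an illustrative rule**

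The protocol sets no responder test. Suppose success needs r of 14 responders at a null rate p0, and d early losses are forced to be responders. Type I error is then P[Bin(14 − d, p0) ≥ r − d].

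| Rule | d = 0 | d = 1 | d = 2 | d = 3 |
|---|---|---|---|---|
| p0 = 30%, r = 8 | 3.2% | 6.2% | 11.8% | 21.0% |
| p0 = 50%, r = 11 | 2.9% | 4.6% | 7.3% | 11.3% |

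**5. Continuous scores in the ANCOVA**

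Let mean decline over 52 weeks be D, linear, and equal in those lost and those who stay. With 3 of 14 carried from baseline, the observed mean decline is (11/14) × D = 0.79 D. With 3 of 14 carried from week 26 it is (1 − (3/14) × 0.5) × D = 0.89 D. The direction is the same as for the responder rate, and the shrinkage is larger if faster decliners are the ones lost.

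**The case against.** The strongest reply is that the problem may never arise. Section 2.12 expects good retention, because the hospital is the national reference centre and patients know the investigator well. With complete week-52 data the choice of imputation has no effect. That stands, and it limits the expected size. It does not make the label right.

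The wording of section 2.16 is also tentative, and the article presents a small phase II study that needs confirmation. Both are true. Yet this is the only technique named, and its stated direction is wrong as written, so deferring details to an analysis plan does not cure it.

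A reader might infer three stronger things that the documents do not support:

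- *Every dropout or untestable patient becomes a responder.* This is certain only when no post-baseline battery exists.
- *Each early loss inflates the rate by 7.1 points.* That is the gap between two extreme rules. It equals the bias only if every lost patient would have deteriorated.
- *Counting missing as non-response gives the true rate.* If lost patients would have responded like completers (60%), that rule gives 47.1%, which is 12.9 points too low and further from the truth than 68.6%.

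Section 2.16 does not say whether baseline values may be carried. If only post-baseline values were, early losses would leave the responder rate, which becomes 6.6/11 = 60%: still at or above the 47.1% to 60% range, and again not conservative.

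Finally, section 2.14 names an ANCOVA, not a responder test. The objection is fair for the type I error figures, which are illustrative, but carried-forward scores are pulled toward baseline in the ANCOVA as well.

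**Conclusion.** The point holds in this form: whenever week-52 data are missing, carrying the last observation forward leans toward efficacy, and the claim that it is conservative is wrong. It also conflicts with the condition that section 2.16 itself sets, and the justification presupposes the treatment effect.

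The direction follows from the protocol's own account of the disease, endpoint, visit schedule and single arm. The size does not, because no dropout or response rate is given. Under 60% completer response and 3 of 14 early losses, the bias is about 2.9 to 7.1 points per early loss, or 8.6 to 21.4 points in total. It is zero without missing data. For losses after week 26 the bias is likely but not automatic.

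**What to change.** In section 2.16, delete the description of the technique as conservative and do not use it as the main method. Then:

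- **Responder rate:** count a patient without an evaluable week-52 battery as a non-responder, and state that this is the conservative analysis. Show the carried-forward result only as a labelled optimistic bound, so that the two bracket the answer.
- **Continuous scores:** replace carried-forward values with a repeated-measures mixed model on the baseline, week-26 and week-52 assessments.
- **Data collection:** still seek the week-52 assessment in patients who stop efavirenz, which reduces the need for imputation.

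Other choices are defensible, but the method should be fixed before outcome data are seen. The cost is mainly a change of wording, plus continued follow-up of patients who stop. The statistical cost is that the reported responder rate may be less favourable, and the worst-case rule can understate it; that is why both bounds should be shown.

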### 2.17. Oversight and monitoring

#### 2.17.1. Composition of the data monitoring committee, its role and reporting structure.

A Data Safety Monitoring Committee will be established for this trial and will consist of members of the study team and third-party pharmacovigilance experts (from the BUH). The data safety monitoring committee will evaluate all the available EFV safety data at each study visit performed during the trial.

During the development of the study, the sponsor will prepare Drug Safety Update Reports (DSURs) annually, following the recommendations of the ICH E2F guideline, and present them to the regulatory authorities and the IRB following the calendar established in the current legislation.

The sponsor will inform the investigators of any new safety information that could jeopardize the patients’ safety as soon as possible. The investigators will also be notified of any modification to the study protocol.

### 2.18. Description of any interim analyses and stopping guideline

No interim analyses have been planned for this trial.

### 2.19. Adverse event reporting and harms

Given that EFV is an authorized medicinal product, the SmPC will be used as the Reference Safety Information.

The investigators will systematically monitor and collect the AEs from the moment of signing the written informed consent to the patient’s last follow-up visit. AEs will be recorded in the patient’s medical record, stating the causality assessment for EFV. AEs related to the EFV will be collected through the eCRF whenever they are serious (SAEs) or AEs of special interest.

The investigators must provide a thorough description of the event, including start and end dates, an intensity assessment (mild, moderate, or severe), measures taken to mitigate it (e.g., none, EFV withdrawal, the medication used to treat the AE), and a causality assessment for EFV.

Any AE or clinically relevant lab abnormality will be followed until satisfactory resolution, stabilization, or until clinical judgment indicates it has an alternative cause and no further assessment is needed.

The investigator must notify the contracted contract research organization of any SAE (including death from any cause) in less than 24 hour after becoming aware of it, regardless of its relationship with EFV. This will be done by sending a specific notification form by fax or email.

Any suspected unexpected serious adverse reaction (i.e., those not reported in the Reference Safety Information) will be of expedited reporting as per the current Spanish (Royal Decree 1090/2015) and European legislation (Regulation EU 536/2014).

For the purpose of this trial, we consider as AEs of special interests laboratory abnormalities in plasma liver enzymes (aspartate aminotransferase and alanine aminotransferase > 2× upper limits of normal).

In the event of a pregnancy during the study, the EFV will be immediately withdrawn. The investigator must notify the sponsor within 24 hours of becoming aware of the event. Appropriate medical assistance will be offered to the patient. These patients will be asked to sign a specific written informed consent allowing the investigators to collect pregnancy-related data. The patient will be followed until the delivery date; if the outcome meets SAE criteria, the investigators will follow the procedures explained before for SAE notification.

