#### 2.2.1. Inclusion criteria.

Patients must:

•Be at least 14 years of age, of both genders.•Be diagnosed with adult-onset NPC based on a genetic study with 2 genetic mutations related to this disorder OR 1 genetic change, 1 positive filipin stain, and a positive biomarker.•Have mild to moderate cognitive impairment with a global Clinical Dementia Rating (CDR) score of 0.5 to 2 and/or a CDR-SoB ≤ 12.•Have the capacity (at the investigator’s discretion) to understand the nature and risks of the trial and the relevant information given, the capacity to decide whether to participate, and sign the written informed consent.•Have a live-in caregiver available more than 5 days a week that can inform the patient’s medical situation, understand the nature and risks of the trial, and sign the written informed consent.•Be proficient in Spanish (the language in which cognitive tests will be conducted).•Have sufficient visual and auditory acuity for understanding explanations given and neuropsychological tests.•Have a minimum 8 years of schooling.•Be on Miglustat treatment (only treatment indicated for NPC) with a stable dose for the last 3 months.•In the case of women of child-bearing potential (i.e., the period between menarche and menopause), have a negative pregnancy test.•In the case of women of child-bearing potential, commit to use highly effective contraceptive measures, which include barrier methods in combination with other contraceptive measures (e.g., oral, or other hormonal contraceptives) or commit to sexual abstinence until at least 12 weeks after the final dose of EFV.•In the case of male patients, commit to use barrier contraceptives (condoms) until at least 12 weeks after the final dose of EFV.•Sign the written informed consent.

***Note***: Although the primary target population of the study is patients with adult-onset NPC (i.e., patients > 16 years old), we will also enroll patients aged between 14 and 16 years old (patients with late juvenile-onset NPC). The justification for including the late juvenile population (between 14 and 16 years old) in the study is that NPC also causes cognitive impairment in this age interval.

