### 2.3. Interventions

The study intervention is EFV. All patients will be treated orally with 25 mg/d of EFV for 52 weeks (1 year), in addition to SoC. Despite this established 25 mg/d dose, successive blood analyses will be performed during the trial, and those patients with no evidence of a blood 24-OH-Cholesterol increase ≥ 1.5 times their baseline levels will have their EFV dose increased up to 200 mg/d.

According to the SmPC, the recommended antiretroviral dose of EFV for adults is 600 mg/d PO, combined with nucleoside reverse transcriptase antiretroviral inhibitor with or without a protease inhibitor. The dose selected for this trial (25 mg/d) is the 1 administered to the pediatric population with 3.5 to <5 kg of weight. Also, as recommended by the SmPC, patients will be advised to take the medication at bedtime.

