#### 2.7.1. Study procedure.

Study candidates will be screened during visit 1. Those who meet all the inclusion criteria and none of the exclusion criteria will be invited to participate. Both patient and caregiver must sign the written informed consent, a sine qua non condition for enrollment. Seven study visits will be performed for enrolled patients, and all the information detailed in Table 3 will be gathered.

**Table 3 T3:** Participant timeline.

	Visit 1 (baseline visit)	Visit 2	Visit 2.1	Visit 3	Visit 4	Visit 5	Visit 6
	Screening and enrollment	Start of treatment					End of treatment
	−60/−30 d	Day 0 (Wk 0)	Wk 4 ± 3 d after visit 2	Wk 13 ± 1 wk after visit 2	Wk 26 ± 1 wk after visit 2	Wk 39 ± 1 wk after visit 2	Wk 52 ± 2 wks after visit 2
**Inclusion/exclusion criteria**	✓	✓					
**Written informed consent**	✓						
**Demographic data***	✓						
**Vital signs (BP, HR, T, RR) and body weight**	✓	✓	✓	✓	✓	✓	✓
**Physical examination**	✓	✓	✓	✓	✓	✓	✓
**Neurological examination** ‡	✓	✓	✓	✓	✓	✓	✓
**Neuropsychological assessment** §	✓				✓		✓
**General blood tests** ‖	✓			✓	✓	✓	✓
**Biomarkers:** **24-OH-cholesterol**	✓			✓	✓	✓	✓
**Biomarkers:** **Oxysterols** **Lyso-sm-509**	✓				✓		✓
**EKG**	✓			✓	✓	✓	✓
**Medication dispensing**		✓		✓	✓	✓	✓
**Brain MRI**	✓						✓
**Brain ^18^FDG-PET scan**	✓				✓		✓
**Oculography**	✓				✓		✓
**Abdominal ultrasound**	✓				✓		✓
**Lumbar puncture**		✓†					✓†
**AE recording**	✓	✓	✓	✓	✓	✓	✓
**Concomitant medication recording**	✓	✓	✓	✓	✓	✓	✓
**Patient’s journal**		✓		✓	✓	✓	✓
**Pregnancy test**	✓	✓		✓	✓	✓	✓

AE = adverse event, BP = blood pressure, EKG = electrocardiogram, HR = heart rate, MRI = magnetic resonance imaging, RR = respiratory rate, T = temperature.

(1) Includes genetic diagnosis.

‡ Includes Ataxia Scale (SARA), Dysphagia Scale (EAT-10), Pineda Disability Scale.

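### Contraception is required for 12 weeks after the last dose, but scheduled AE recording and pregnancy testing end at the end-of-treatment visit, leaving about 10 to 12 weeks of that window with no scheduled observation

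*Protocol article*

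**What the plan says.** All references are to the Protocol article.

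- **Contraception (2.2.1).** Women of child-bearing potential must use highly effective contraception or "commit to sexual abstinence until at least 12 weeks after the final dose of EFV". Men must "commit to use barrier contraceptives (condoms) until at least 12 weeks after the final dose of EFV".
- **Treatment length (2.3).** "All patients will be treated orally with 25 mg/d of EFV for 52 weeks (1 year), in addition to SoC".
- **Visits (2.7.1, Table 3).** "Seven study visits will be performed for enrolled patients": Visits 1, 2, 2.1, 3, 4, 5 and 6. Visit 6 is headed as the end of treatment and timed at "Wk 52 ± 2 wks after visit 2". No column follows it. AE recording is ticked at all seven visits. The "Pregnancy test" row is ticked at Visits 1, 2, 3, 4, 5 and 6. The medication dispensing row is ticked at Visits 2, 3, 4, 5 and 6.
- **AE collection (2.19).** Investigators are to "systematically monitor and collect the AEs from the moment of signing the written informed consent to the patient’s last follow-up visit". The section gives no date for that last visit.
- **Pregnancy (2.19 and 2.4).** "In the event of a pregnancy during the study, the EFV will be immediately withdrawn". The sponsor is then notified within 24 hours and the patient is followed to delivery. Section 2.4 lists a participant's pregnancy among the reasons to stop EFV. Neither section mentions the partner of a male patient.
- **Other safety provisions.** Known AEs are followed to resolution or stabilization, and SAEs are notified within 24 hours of awareness (2.19). The safety committee evaluates the safety data at each study visit (2.17.1). The principal investigator stays the patients' physician after the trial (2.26).

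**The concern.** Three stated rules do not fit together. The contraception rule looks 12 weeks or more past the last dose. The visit schedule stops at about the last dose. The AE rule ends at a follow-up visit that the schedule does not contain unless it means Visit 6.

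Safety is part of the primary objective (Table 1). If the trial asks patients to avoid conception for 12 weeks after stopping, the natural question at the end is whether any pregnancy occurred in that time. As scheduled, nobody asks. An AE that starts after Visit 6 is in the same position: whether it enters the trial data depends on how the last follow-up visit is read and on whether the investigator happens to hear of it.

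The dispensing tick at Visit 6 adds to the uncertainty. If drug really were handed out then, exposure would run past the last visit and the contraception window would move later with it.

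**Working it through.** The document gives no figure to reproduce here. The check compares the end of the contraception window with the last scheduled observation.

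**Inputs**

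- Treatment length: 52 weeks (2.3).
- Contraception after the last dose: a minimum of 12 weeks (2.2.1).
- Last scheduled visit: week 52 ± 2 weeks, so weeks 50 to 54 (Table 3).
- Last AE recording and last pregnancy test: Visit 6 (Table 3).

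**Step 1: end of the contraception window.** Last dose + 12 = 52 + 12 = week 64 at the earliest.

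**Step 2: part of the window after the last scheduled visit.**

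| Visit 6 | Last dose | Window ends | Last visit to end of window | Post-dose weeks with no scheduled observation |
|---|---|---|---|---|
| Week 52 | Week 52 | Week 64 | 64 − 52 = 12 weeks | 12 |
| Week 54 | Week 52 | Week 64 | 64 − 54 = 10 weeks | 10 |
| Week 50 | Week 52 | Week 64 | 64 − 50 = 14 weeks | 12 |
| Any allowed week | Day of Visit 6 | Visit 6 + 12 | 12 weeks | 12 |

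The unscheduled part of the post-dose window is therefore 10 to 12 weeks. At most 2 of the 12 weeks are covered, and only when Visit 6 falls late.

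**Step 3: comparison with the on-treatment schedule.** After week 0, pregnancy tests fall at weeks 13, 26, 39 and 52, which is every 13 weeks. The 12-week window is about one such interval, so a single contact at its end would roughly continue the spacing already in use.

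**Step 4: do the other provisions fill the gap?**

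- Following AEs to resolution and pregnancies to delivery applies once the event is known.
- SAE notification is triggered by awareness. It has no stated end date, but it schedules no contact.
- Care by the same physician after the trial is ordinary care, not trial data collection.
- Committee review is tied to study visits, and none follows Visit 6.

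None of these actively seeks a new pregnancy or a new AE in the window.

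**Step 5: patients who stop early.** Their 12 weeks start at their own last dose. If they keep attending the planned visits and stop by week 40 (52 − 12), the window closes by nominal Visit 6. If they leave the schedule, it may be wholly uncovered. The article does not say which applies.

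**The case against.** The strongest reply is that the AE sentence never says collection ends with treatment. It names a last follow-up visit, and equating that with Visit 6 is an inference. The article also condenses a full protocol that is not shown. The inference is sound all the same: the article gives the number of visits, lists them all, and places none after Visit 6. The visit count, the contraception period and the AE end point are all printed, so this is a mismatch between stated rules and not missing detail.

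Other parts of the reply stand and limit the point. A reader might infer any of the following, and the document does not support them:

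- **That the window goes entirely unobserved.** Known AEs and pregnancies are followed, SAEs are notified on awareness, and the patients stay under the same physician. What is missing is scheduled observation.
- **That 12/(52 + 12) = 18.75% of an at-risk period for AEs is unwatched in every patient.** The 12 weeks is a contraception commitment. It is nowhere called an AE risk window, and among women it binds only those of child-bearing potential. The mismatch bears most directly on pregnancy surveillance. The gap in general AE collection rests on the undefined last follow-up visit.
- **That partner pregnancies are proven to be uncovered.** The article is silent on them, and the full protocol may not be. This is a point to state, not an established omission.
- **That particular harms emerge after stopping.** The document describes none with onset after the last dose.
- **That patients leave Visit 6 with more drug.** The dispensing row has the same ticks as the patient's journal row, and the article also provides for empty-box review and records of returns, so the tick may stand for accountability.

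**Conclusion.** The concern holds as a mismatch between sections 2.2.1, 2.7.1 and 2.19. About 10 to 12 weeks of the contraception window that the protocol itself sets have no scheduled pregnancy test or AE recording, and the visit that ends AE collection has no post-treatment counterpart in Table 3. The figure assumes dosing to week 52 or to the day of Visit 6, Visit 6 within its ± 2 weeks, and that the last follow-up visit is Visit 6. If the full protocol defines a later visit, the gap narrows or closes and the article's Table 3 is what needs correcting.

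No efficacy estimate or week-52 analysis is affected. The Visit 6 dispensing entry and the stated 52 weeks of treatment must be reconciled; the document does not allow a choice between readings. This is a cheap improvement to safety data collection and does not threaten the trial's validity.

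**What to change.** 1. Define the last follow-up visit in section 2.19 and show it in Table 3.
2. Reconcile sections 2.2.1, 2.7.1 and 2.19 so that pregnancy and AE collection match the contraception window already stated. One way is a single remote safety contact per patient at the end of that window, counted from each patient's own last dose so that early stoppers are included.
3. State whether the pregnancy procedure in section 2.19 covers pregnancies after the last dose and in partners of male patients.
4. Reconcile the Visit 6 dispensing tick with the stated treatment length.

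**Cost.** Amendment wording and, with 14 expected patients (2.8), about 14 extra contacts. Last-patient-out moves later by about 12 weeks for safety data only; the week-52 efficacy read-out keeps its date.
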